**Figure 2 figure2:**
[figure not shown]
Screenshot from the VoiceAdapt app displaying the summary screen of the Semantic Feature Analysis protocol.

**Figure 3 figure3:**
[figure not shown]
Screenshot from the VoiceAdapt app displaying the summary screen of the Phonological Components Analysis protocol.

**Figure 4 figure4:**
[figure not shown]
Screenshot from the VoiceAdapt app displaying the user help screen.

### Duration

The participants will take part in the study for approximately 13 weeks once enrolled. Pretreatment assessment will take place in Week 1, followed by 5 weeks of engagement in Phase 1 (treatment or control). Midpoint assessments will take place in Week 7, followed by 5 weeks of engagement in Phase 2 (crossover into control or treatment). Final assessments will take place in Week 13 following study enrollment.

### Measures

Efficacy will be monitored by the scores on primary and secondary outcome measures. The primary outcome measure will be the BNT [25] to measure naming; secondary outcome measures will be the WAB-R [26]; Stroke and Aphasia Quality of Life Scale-39 (SAQOL-39) [27] to measure quality of life; and Communication Effectiveness Index (CETI) [28] to measure the communication capabilities of the participants with aphasia and their partners’ perception of the participants’ communication. In addition to the primary and secondary outcome measures, the System Usability Scale (SUS) [29], Situational Motivation Scale (SIMS) [30], and a posttreatment questionnaire specific to app usage will be administered to all participants. In addition, the in-app parameters evaluating aspects such as the amount of time spent on training per session, total amount of time spent on training over the study duration, etc will also be measured for future analysis.

### Sample Size Determination

The planned enrollment for the study is 80 (ie, 40 at each of the two sites in Canada). The sample size calculation is based on the medium effect sizes estimated in our study according to previous results. Accounting for a dropout rate of approximately 10%, we need to include 79 people with aphasia; thus, we plan to enroll 80 people with aphasia. We will conduct an intention to treat analysis and include all the randomized participants in our analyses.

### Analytic Strategy

Mixed-effects regression will be used to analyze the 2 × 2 crossover trial with one baseline [31]. The analysis will include covariate adjustments for variables such as the recruitment site and participant characteristics (eg, sex, age, hours of training, assessors, and caregiver characteristics). Adjustment can increase the precision of the treatment effect estimates and confirm whether training was equally efficacious across covariates (ie, using covariates by treatment interaction) and whether the retention of improvement was equal across covariates (ie, covariates by carryover interaction). Mixed-effects regression can also account for hierarchical sampling, which is important if participants within sites are more similar than if they were randomly chosen. If carryover is detected, we will also estimate the treatment effects after excluding the Period 2 assessments affected by carryover.

The Mauchly test will be used to evaluate whether the sphericity assumption is tenable. If the variances are unequal, we will disaggregate the analysis and use paired and two-group *t* tests as appropriate to estimate the treatment, carryover, and period effects; if covariate adjustment is required, these contrasts will be evaluated using mixed-effects regression while also accounting for hierarchical sampling.

Interim analyses will be conducted when quarterly enrollment targets are met (ie, 20, 40, and 60 participants).

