**Methods:**

A multicenter RCT is being conducted at two locations within Canada. A total of 80 people with aphasia will be recruited to participate in a two-arm, waitlist-controlled, crossover group RCT. After baseline assessment, participants will be randomized into an intervention group or a waitlist control group. The intervention group participants will engage in 5 weeks of training with the app, followed by posttreatment and follow-up assessments after an additional 5 weeks. Those in the waitlist control group will have no training for 5 weeks; this is followed by pretreatment assessment, training for 5 weeks, and posttreatment assessment. All trial procedures are being conducted remotely given the COVID-19 pandemic.

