### Study Design

The RCT will have a two-arm, randomized, waitlist-controlled, crossover group design. In Phase 1, people with aphasia randomized to the intervention group will train with VoiceAdapt. The control group will be a waitlist treatment-deferred group. In Phase 2, the control group will train with VoiceAdapt (see Figure 1). Participants will be randomized to groups according to a computer-generated randomization list.

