### Intervention

The app intervention comprises naming exercises based on evidence-based anomia treatments, SFA and PCA, delivered on a mobile tablet. The exercises involve the presentation of a colored picture and a series of prompts designed to engage the people with aphasia in providing semantic features (eg, “What is it used for?” [action]; “What does it look like?” [properties]); or phonological components (eg, “What sound does it start with?” [first sound]; “What is a rhyming word?” [rhyme]). Figures 2 and 3 display summary screens reviewing the generated semantic and phonologic features of the target items, respectively (Additional screenshots of the app are displayed in Multimedia Appendix 1). A help screen also reminds users of the various features (Figure 4). The patient’s voice is recorded and used as the input for the app. The app is designed to maximize user engagement through UCD principles. People with aphasia randomized to the VoiceAdapt treatment group will be instructed to practice using the app during weekdays for one hour per day for 5 weeks. The people with aphasia will have the option of downloading the app on their own tablets from a link provided by the researchers, or the researchers will provide them with tablets with the app loaded. Research staff will check in and monitor progress through email or telephone/video calls on a weekly basis.

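### Hours of training is a post-randomisation dose measure listed as a baseline-type covariate; if it enters the efficacy model per period, the treatment coefficient becomes the effect at zero hours of use

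*Protocol article*

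**What the plan says.** All references are to the protocol article.

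- **Analytic Strategy.** The 2 × 2 crossover is to be analysed by mixed-effects regression with one baseline. "The analysis will include covariate adjustments for variables such as the recruitment site" and, in the same sentence, for "participant characteristics (eg, sex, age, hours of training, assessors, and caregiver characteristics". The adjustment is not labelled as a sensitivity or exploratory analysis.
- **Purpose of adjustment (same section).** The first purpose is precision: "Adjustment can increase the precision of the treatment effect estimates". The second is effect modification, to "confirm whether training was equally efficacious across covariates (ie, using covariates by treatment interaction".
- **Intervention.** Trained participants are told to "practice using the app during weekdays for one hour per day for 5 weeks". The Discussion gives the dose as 25 hours.
- **Abstract, Methods.** "Those in the waitlist control group will have no training for 5 weeks".
- **Study Design.** "In Phase 2, the control group will train with VoiceAdapt".
- **Measures.** In-app training time, per session and in total over the study, is recorded for later analysis.
- **Sample Size Determination.** "We will conduct an intention to treat analysis and include all the randomized participants in our analyses".

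**The concern.** Covariate adjustment sharpens a randomised comparison when the covariate is fixed before randomisation. Age, sex and site qualify. Hours of training does not: it records how much of the intervention a person took. Adjusting for it can hold constant the route by which the app is meant to work, and it introduces a variable that nearly duplicates the treatment indicator.

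The primary estimate on the Boston Naming Test is at stake. In some forms of the model the reported coefficient would no longer answer whether being given the app improves naming. Its standard error would grow, against the stated aim of better precision. An app that works could then be reported as showing no effect. Including every randomised participant does not repair this, because the quantity estimated is no longer the effect of assignment.

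**Working it through.** **Inputs from the article.** Instructed dose: 1 hour × 5 weekdays × 5 weeks = 25 hours, which agrees with the Discussion. Enrolment 80 with about 10% dropout: 80 × 0.9 = 72 completers, or 36 per arm. Hours in an untrained period: 0.

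**Assumed inputs (not in the article).** True effect 0.5 SD; mean hours m = 20, SD s = 5 or 6; within-participant correlation about 0.5 in the crossover; baseline correlation 0.8 in one Period 1 check; no carryover.

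**1. Meaning of the coefficient.** Let T = 1 in a trained period and 0 otherwise, and let h be a participant's hours when trained. Hours per period is then H = T × h. If the benefit at h hours is a + b·h, the effect of assignment is a + b·m. A model with T and H returns a as the coefficient of T, which is the effect at zero hours.

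| Share of benefit through dose | b per hour | Coefficient of T |
|---|---|---|
| All | 0.5/20 = 0.025 | 0.5 − 0.025 × 20 = 0 |
| Half | 0.25/20 = 0.0125 | 0.5 − 0.0125 × 20 = 0.25 |
| None | 0 | 0.5 |

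**2. Precision, Period 1 comparison with equal arms.** The variance of H is 0.25m² between arms plus 0.5s² within, so VIF = 1 + m²/(2s²).

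- m = 20, s = 6: 1 + 400/72 = 6.6; SE × 2.6.
- m = 20, s = 5: 1 + 400/50 = 9.0; SE × 3.0.
- Range: m = 15, s = 8 gives 1 + 225/128 = 2.8 (SE × 1.7); m = 25, s = 2.5 gives 1 + 625/12.5 = 51 (SE × 7.1).

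**3. Precision, crossover.** In within-participant differences (trained minus untrained), the coefficient is the intercept at h = 0, and its variance is multiplied by 1 + m²/s². With m = 20 and s = 5 this is 17, so SE × 4.1.

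**4. Simulation with per-period hours.**

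- Crossover, 72 completers, s = 5. Without hours: 0.50 (SE 0.12), power 98 to 99%. With hours: −0.01, 0.24 and 0.51 for all, half and none through dose; SE about 0.5; power 5 to 19%.
- Period 1 only, s = 5. Without hours: 0.50 (SE 0.22). With hours and all benefit through dose: 0.00 (SE 0.67).
- Period 1 only, s = 6, baseline correlation 0.8. Without hours: 0.50 (SE 0.14), power 93%. With hours: about 0, 0.25 and 0.50; SE about 0.375; power 5%, 10% and 27%.

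**5. Interaction under per-period coding.** H × T = T × h × T = T × h = H. The interaction column is identical to the main effect, so it cannot be estimated.

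**6. Participant-total hours.** A total is constant within a participant. As a main effect it drops out of the within-participant contrast, which stays at 0.50. With an uncentred total-hours-by-treatment term, the product T × h is the same column as H, and the treatment coefficient is again the effect at zero hours (−0.01 when all benefit is through dose). With a centred term it stays at 0.50.

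**The case against.** The strongest reply is that the article does not fix the coding. Hours stands beside sex and age, and Measures records a total over the study, so one total per participant is a natural reading. Both arms eventually train, so the total is not zero for the waitlist arm. As a main effect it leaves the within-participant contrast alone. Even in a Period 1 comparison it left the estimate at 0.50 to 0.51 with SE 0.14, assuming similar hours in both arms and hours unrelated to prognosis. This stands, and it makes the damage conditional. It does not justify keeping the variable: in its harmless form it adds essentially nothing to the contrast, and the text does not exclude the harmful forms.

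The covariate list is also illustrative, in a condensed article, and the t-test fallback makes adjustment conditional. That limits the weight of the point. It is still not an omission that an unseen analysis plan would fill, because the article names the variable.

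Three stronger readings are tempting, and the article does not support them:

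- *Hours is zero in the waitlist arm throughout.* This is true only of Phase 1; that arm trains in Phase 2.
- *Adjustment necessarily removes the treatment effect.* This needs per-period coding or an uncentred interaction, and benefit that works wholly through dose. A Period 1 comparison would arise only as an additional estimate if carryover is detected.
- *Adjusting for caregiver characteristics would drop participants and breach intention to treat.* Nothing in the article says that any participant lacks a caregiver or would be excluded for that reason.

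**Conclusion.** The point holds in conditional form. Listing hours of training as a participant characteristic to adjust for is wrong as written, because it is the dose received after randomisation. Under per-period coding, including a Period 1 analysis after carryover, or as a total with an uncentred interaction, the treatment coefficient is the effect at zero hours. At assumed hours of 20 (SD 5 to 6), the SE under per-period coding is about 2.6 to 4 times larger, and an assumed 0.5 SD effect is estimated at about 0, 0.25 or 0.5 according to whether all, half or none of the benefit works through dose. Neither stated purpose of adjustment is then met for this covariate: precision falls and the interaction is not estimable. As a participant-total main effect it does no harm to the within-participant contrast and brings it essentially no gain.

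The article gives no numerical effect size, correlation or expected spread of hours. The power figures illustrate the mechanism and are not predictions for this trial. The direction of the precision loss under per-period coding does not depend on those inputs: both inflation factors exceed 1 whenever mean hours is above zero.

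**What to change.** In Analytic Strategy, delete hours of training from the covariates of the efficacy model. State that adjustment is limited to variables fixed before randomisation, for example site, age, sex and the baseline score already in the model. Add that the relation between hours of training and outcome will be reported separately and labelled exploratory, using the in-app time data already collected under Measures.

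The cost is a sentence or two in the analysis section. It needs no new data and no change to conduct or sample size. It should be settled before the outcome data are analysed.

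### A Mauchly sphericity pretest, which a mixed model does not need, decides whether the primary analysis is broken up into t tests, and the text does not fix which t test then estimates the treatment effect

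*Protocol article*

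**What the plan says.** Everything on this point is in the protocol article, Methods, mostly under Analytic Strategy.

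- Main analysis: "Mixed-effects regression will be used to analyze the 2 × 2 crossover trial with one baseline".
- Covariates, stated without condition: "The analysis will include covariate adjustments for variables such as the recruitment site and participant characteristics".
- Pretest and trigger: "The Mauchly test will be used to evaluate whether the sphericity assumption is tenable. If the variances are unequal, we will disaggregate the analysis".
- Fallback, of the paired and the two-group kind: "tests as appropriate to estimate the treatment, carryover, and period effects".
- A qualifier closing the same sentence: "if covariate adjustment is required, these contrasts will be evaluated using mixed-effects regression while also accounting for hierarchical sampling".
- Analysis population, under Sample Size Determination: the plan is intention to treat and will "include all the randomized participants in our analyses", with dropout expected at about 10%.

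The Duration section sets three assessments, in Weeks 1, 7 and 13.

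**The concern.** The gate brings an assumption of one method (univariate repeated-measures ANOVA) into another (mixed-effects regression). A mixed model depends on something like sphericity only if its covariance is restricted to compound symmetry. The remedy is then a freer covariance structure within the same model.

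The test and its trigger also do not match. The text tests sphericity but acts on unequal variances, which is a different condition.

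At stake is the primary outcome, the Boston Naming Test. A test run on the trial data would choose the form of the efficacy analysis, and the alternative branch contains several t tests that differ in power, in who is included and, if gains persist, in what they estimate. The two statements on covariates leave open whether that branch can ever be reached.

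**Working it through.** **Stated figures.** The article attaches no number to this rule, so there is none to reproduce. From the documents I take 80 enrolled and about 10% dropout: 80 × 0.9 = 72 completers, 36 per arm, with three visits. Assumed, because the documents do not give them: Mauchly level 0.05, effect 0.5 SD, the correlations and SD ratios below, and any practice gain.

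**1. What Mauchly's test examines.** With unit variances, the variance of the difference between two visits is 2(1 − ρ). Sphericity requires these to be equal for every pair of visits.
- If only the two post-baseline periods are modelled there is one difference and one variance, so nothing can be compared and the test is vacuous. It has content only if baseline is a third repeated measure.
- With correlations 0.9/0.8/0.9 (Weeks 1–7, 1–13, 7–13) the variances of differences are 0.2, 0.4 and 0.2. Sphericity fails although all three visit variances are equal.

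**2. How often the gate would open.** Simulated trials, 72 participants, equal variances, residuals from arm means:

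| Correlations (1–7 / 1–13 / 7–13) | Mauchly rejects |
|---|---|
| all equal (compound symmetry) | about 5% |
| 0.9 / 0.88 / 0.9 | 14% |
| 0.8 / 0.75 / 0.8 | 19% |
| 0.9 / 0.85 / 0.9 | about 58% |
| 0.6 / 0.36 / 0.6 | 73% |
| 0.8 / 0.64 / 0.8 | 92% |
| 0.9 / 0.8 / 0.9 | 99% |

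Conversely, with variances that do differ (SDs 1, 1.15, 1.3; equal correlations of 0.6 or 0.8), the test rejects in only 17–20% of trials. It therefore tracks the stated trigger poorly in both directions.

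**3. Whether leaving the model is needed.** A baseline-adjusted comparison at Week 7, standing in for a mixed model with unstructured covariance, kept its type I error at 0.045 to 0.055 under compound symmetry, decaying correlation and unequal variances alike.

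**4. What the choice of t test does.** Two-sided 0.05, 36 per arm, noncentrality d√(n/2) = d√18 = 4.243d.
- Two-group t on Week 7 score: d = 0.5, noncentrality 2.12, power 0.55.
- Two-group t on change, ρ = 0.8: d = 0.5/√(2 × 0.2) = 0.791, noncentrality 3.35, power 0.91.
- Baseline-adjusted, ρ = 0.8: d = 0.5/√(1 − 0.64) = 0.833, noncentrality 3.54, power 0.94.
- At ρ = 0.6 the three powers are 0.55, 0.65 and 0.74.
- Two-group t on period differences (Week 7 minus Week 13): power 0.96 to 1.00 if no gain is retained. If the first arm keeps a gain δ, its mean period difference is δ − δ = 0 and the waitlist arm's is 0 − δ = −δ. Half the contrast is δ/2, so a true 0.50 is estimated as 0.25.
- Paired t, only if used as a within-arm pre-post test of treatment: noncentrality is gain/√(2(1 − ρ)) × √36. With no treatment effect, a practice gain of 0.1 SD is significant in 15% (ρ = 0.8) to 26% (ρ = 0.9) of trials, and a gain of 0.2 SD in 45% to 74%. With a 0.2 SD gain in both arms, the two-group tests stayed at 4.4–5.2%.

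**5. Who is analysed.** A t test on change or on period differences needs two visits per person. With about 10% dropout, up to 80 − 72 = 8 randomised participants could fall out, against the commitment to analyse everyone randomised.

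**6. The covariate statements side by side.** One says the analysis will adjust for covariates. The other keeps the disaggregated contrasts in mixed regression only if adjustment is required. If the first governs, the condition is always met and the t-test branch has no use. If that branch can be reached, the planned adjustment is dropped in it. The article does not say what makes adjustment required.

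**The case against.** The strongest reply is that the sentence does not end with t tests. Its last clause keeps the contrasts in mixed-effects regression when adjustment is required, and adjustment is planned. A failed Mauchly test may then mean only that separate contrasts are fitted by mixed regression, with t tests used seldom or never. This stands. A reader might infer that the mixed model is abandoned, or that covariate adjustment and partial completers will probably be lost. The text supports neither; it supports only that the two covariate statements need reconciling.

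A reader might also infer that the fallback is weaker in general. That holds clearly for a score-only t test. At correlation 0.8 the loss with change scores is small (0.91 against 0.94), and without carryover a period-difference t test is not weaker at all. For carryover, the article also plans a further estimate without the affected Period 2 assessments, which limits the halving if carryover is detected.

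A third tempting reading is that uncontrolled pre-post tests will enter the efficacy evidence. The text names paired tests but never says that a within-arm pre-post test will estimate the treatment effect, and a two-group test on period differences is controlled.

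Finally, covariance structure, degrees of freedom and the matching of tests to contrasts can be left to a statistical analysis plan, and their absence here is no fault. That does not answer the point about the gate, which the article states outright and states wrongly.

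**Conclusion.** The point holds in limited form. As written, a pretest that a suitably specified mixed model does not need, with a trigger it does not measure, decides after the data are seen whether the primary analysis is disaggregated. Under the assumptions above the gate could open in about 5% to 99% of trials. The documents give no correlations that would narrow this range.

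The consequence depends on how the fallback is read. Power could be about 0.55, 0.91 or 0.94 at correlation 0.8, and a period-difference estimate would be halved if the first arm retains its full gain. If planned adjustment governs, the t tests may never be used. The gate then has no bearing on them, but the contradictory covariate wording remains. Loss of control for practice effects is a conditional risk only. This should be corrected, but it does not show that the trial's primary result would be invalid.

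**What to change.** Delete the Mauchly test and the disaggregation rule. Prespecify one mixed model for the Boston Naming Test scores, with:

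- an unstructured covariance over the three visits, so that variances and correlations may differ by visit;
- the planned covariates, named and included without condition, which removes the conflict between the two covariate statements;
- one stated treatment contrast;
- all randomised participants.

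REML estimation with Kenward-Roger degrees of freedom suits a trial of this size. Keep t tests as sensitivity analyses at most, and report within-arm change descriptively.

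The cost is a change of wording and a few more covariance parameters: six for three visits, against two under compound symmetry. That is modest with about 80 participants.

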### Ethics Statement and Consent

This study will be conducted according to Canadian and international standards of Good Clinical Practice for all studies. Applicable government regulations and the University of Toronto and University of Alberta research policies and procedures will also be followed.

This protocol and any amendments to the same will be submitted to the University of Toronto Human Research Ethics Unit (HREU) and University of Alberta Health Research Ethics Board (HREB) for formal approval to conduct the study.

All participants selected for this study will be provided a consent form describing the study and providing sufficient information for them to make an informed decision about their participation in this study. This consent form will be submitted with the protocol for review and approval by the HREU and HREB. The formal consent of a participant, using the HREU- and HREB-approved consent form, will be verbally obtained and recorded before that participant is subjected to any study procedure per HREU- and HREB-approved procedures.

